## Background

Worldwide, colorectal cancer is the third most common type of cancer for men and women [1]. In the Netherlands, about 15.000 people are diagnosed with colorectal cancer each year [2]. Surgery is the cornerstone of treatment in patients with colorectal cancer. However, the 30-day complication rate after elective colorectal resection is approximately one-third [3], including for example an anastomotic leakage, ileus, or wound infection. Colorectal cancer primarily occurs in the elderly. The level of psychophysiological reserve capacity (resilience) and comorbidities affect the tolerance to surgery in older patients [4]. According to the Dutch Surgical Colorectal Audit, approximately 35% of the patients with colorectal cancer are aged between 60 and 70 years, and 40-50% of the patients are aged over 70 years [5]. These older patients more often have a low cardiorespiratory fitness.

In the literature, preoperative cardiorespiratory fitness has consistently been reported to be associated with postoperative outcome in major elective intra-abdominal surgery (e.g., morbidity, mortality, and length of stay) [6]. Cardiorespiratory fitness can be measured objectively using a cardiopulmonary exercise test (CPET) by determining the ventilatory anaerobic threshold (VAT). The VAT is an accurate and repeatable measurement [7] that can be obtained from the CPET, without a learning effect [8]. It is a physiological construct that occurs at submaximal exercise intensity. Hence, the VAT is only marginally influenced by the patient’s ability and motivation to deliver a maximal effort. Previous studies showed that there is a significant association between a low VAT and postoperative complications in major non-cardiac surgery [8–21]. Patients with a VAT < 11 mL/kg/min have a higher likelihood for postoperative complications [17, 22].

The literature shows that high-risk patients (those patients with a higher likelihood of postoperative complications), who participated in a physical exercise training program prior to elective surgery (prehabilitation), improved their cardiorespiratory fitness [23–25], which has led to the hypothesis that postoperative complications can be reduced by prehabilitation [23, 25–27]. Dunne et al. [28] designed a four-week high-intensity interval training program based on the work rate at the VAT for patients prior to hepatic resection. Their aim was to assess feasibility and to improve the preoperative VAT by 1.5 mL/kg/min (a 10% increase). They found their program to be feasible in sedentary healthy volunteers, resulting in a > 10% improvement in cardiorespiratory fitness (VAT). Using preoperative risk stratification, a 10% improvement in cardiorespiratory fitness in patients undergoing hepatic resection would shift 30% of the high-risk patient group to a low-risk patient group [28].

Prehabilitation programs may have beneficial effects on postoperative outcome; however, the effects on physical functioning, morbidity, mortality, and length of stay are inconclusive. In a systematic review of Moran et al. [6] that aimed to assess the ability of prehabilitation to influence postoperative outcome after intra-abdominal surgery, it was concluded that prehabilitation appears to be beneficial in decreasing the incidence of postoperative complications. Additionally, a systematic review of Bruns et al. [29] reported that prehabilitation can improve the physical fitness of older patients undergoing colorectal surgery; however, no significant effect on the reduction of complications or length of stay could be demonstrated. They concluded that previous studies on the effects of prehabilitation in patients undergoing elective colorectal resection provided no clear and complete description of the content and execution of the prehabilitation program, and that in most of these studies no adequate sample size calculation was performed [29]. Hijazi et al. [30] recently performed a systematic review of all comparative studies on prehabilitation versus usual care in patients undergoing abdominal cancer surgery. No significant difference was found in postoperative complications between prehabilitation and usual care groups. They concluded that prehabilitation programs for patients undergoing major abdominal cancer surgery remain heterogeneous in terms of their composition, duration, mode of administration, compliance, and outcomes measures used to quantify their impact. Therefore, the findings and recommendations are limited. They recommended for future research to standardize these aspects prior to the evaluation of the effects of prehabilitation programs on a larger scale [30]. Thus, it remains to be demonstrated whether a prehabilitation program reduces postoperative complications [31]. Previous studies are biased toward selection of patients with low risk of postoperative complications, and it is unlikely that a prehabilitation program of a few weeks will give a clinically relevant improvement of cardiorespiratory fitness in these low-risk patients.

In summary, current studies addressing the effects of prehabilitation on overall postoperative complications in patients with colorectal cancer are inconclusive, opposing, and of low-to-moderate methodological quality and/or therapeutic validity (concept of Hoogeboom et al. [32]). More high-quality studies are needed to validate its use in the preoperative setting [6, 33]. Recently though, it has been demonstrated that personalized prehabilitation reduced the number of patients with postoperative complications by 51% in high-risk patients undergoing elective major abdominal surgery [24]. Nevertheless, the selection of high-risk patients in this study of Barberan-Garcia et al. [24] was not performed by the use of an objective test, such as a preoperative CPET. Based on the previous published work, the current study will be different in several ways: 1) we perform a validated procedure of preoperative risk stratification with each eligible patient, in order to include only patients with a higher risk for postoperative complications based on cardiorespiratory fitness, 2) we preoperatively measure cardiorespiratory fitness objectively by using an evidence-based CPET to assess the VAT for risk stratification, 3) we design a personalized prehabilitation program based on the results of the CPET, 4) we train at a physical therapy practice close to the patient’s home and not at the outpatient clinic of the hospital, as high-risk patients and their informal caregivers are less or even unable and/or less motivated to visit the hospital to train three times a week during the preoperative period, 5) we give an exact description of the content and execution of the prehabilitation program, 6) we select a patient group with a homogeneous diagnosis, that is patients with colorectal cancer or dysplasia only, and 7) we performed an adequate sample size calculation based on previous data on the effect of prehabilitation in patients undergoing elective hepatic resection [25, 28], as well as on the reported complication rates in frail patients undergoing colorectal resection presented by Robinson et al. [34].

The primary objective of this randomized controlled trial is to evaluate the hypothesis that a three-week prehabilitation program (intervention group) will reduce the number of postoperative complications from 50% to 20% in patients with a preoperative VAT < 11 mL/kg/min who will undergo elective colorectal resection for colorectal cancer or dysplasia grade I, II, or III, when compared to usual care (control group).

The secondary objectives are 1) to observe whether changes in preoperative cardiorespiratory fitness occur in the intervention group (prehabilitation, single-arm study design), 2) to evaluate the effect of the prehabilitation program on length of stay, 3) to examine whether patients with a preoperative VAT ≥ 11 mL/kg/min, and who will therefore not be included in the randomized controlled trial, have fewer postoperative complications than patients in the prehabilitation or usual care group (for the prehabilitation group, we will use the post-prehabilitation CPET data), 4) to investigate the value of a limited geriatric assessment in this patient group to perform preoperative risk stratification, and 5) to evaluate the cost-effectiveness of prehabilitation in high-risk patients by performing a cost-effectiveness analysis.

## Methods

### Study design

This study is a multicenter prospective randomized controlled trial. The trial has started in February 2014 and will run till patient inclusion is completed (probably at the end of 2018) at Medisch Spectrum Twente in Enschede and Ziekenhuisgroep Twente in Almelo, two large community teaching hospitals in the eastern part of the Netherlands. In this manuscript, the latest version of the study protocol (version 9, March 2017) is presented. The study is approved by the Medical Ethics Committee Twente in Enschede, the Netherlands (registration number P13-18), and is registered in the Netherlands Trial Register (NTR4032). Protocol amendments will be agreed and approved by the Medical Ethics Committee Twente.

### Participants

To be eligible to participate in this study, a patient must meet all of the following inclusion criteria: 1) ≥ 60 years, 2) colorectal cancer or premalignant colorectal lesions (dysplasia grade I, II, or III) requiring colorectal resection, 3) undergoing elective colorectal resection at Medisch Spectrum Twente, Enschede, or at Ziekenhuisgroep Twente, Almelo, 4) having a life expectancy of more than 6 months as estimated by the surgeon, 5) has given informed consent to participate in this study, 6) a metabolic equivalents of task (MET) score ≤ 7 on the veterans-specific activity questionnaire (VSAQ), 7) able to perform a CPET, 8) a VAT < 11 mL/kg/min as measured at the baseline CPET, and 9) willing to perform prehabilitation at a community physical therapy practice in the adherence area of both hospitals. All patients not meeting these criteria will not be considered for inclusion. Participants can leave the study at any time for any reason if they wish to do so, without any consequences. The investigator can decide to withdraw a participant from the study for urgent medical reasons.

### Recruitment

All patients will be identified at the multi-disciplinary oncology meetings, and will be evaluated at the outpatient clinic by the surgeon or surgical resident. As most postoperative complications are to be expected in patients with a low cardiorespiratory fitness [6], we aim to include only patients who are expected to be unfit in the pre-study assessments. To select patients with a potentially low cardiorespiratory fitness, all patients identified at the multi-disciplinary oncology meeting are asked to fill out the VSAQ [35]. The VSAQ links physical activities to a particular MET score, based on the Compendium of Physical Activities [36]. Snowden et al. [14] found that patients with a VSAQ score > 7 METs are most likely not to have major postoperative complications. Therefore, we define a low perceived cardiorespiratory fitness as a VSAQ score ≤ 7 METs.

Patients with a VSAQ score ≤ 7 METs will receive very limited information about the study. They will be asked to participate in a study addressing the role of cardiorespiratory fitness (assessed with a CPET) on postoperative complications following colorectal resection. If informed consent is obtained (Additional file 1), the patient will be randomized to the intervention group (prehabilitation) or the control group (usual care), and they will undergo a CPET to obtain objective information about their cardiorespiratory fitness, as standard work-up. Eventually, patients with a VAT < 11 mL/kg/min can participate in the study, whereas randomized patients with a VAT ≥ 11 mL/kg/min cannot participate in the study (in the intervention group, nor in the usual care group). See Fig. 1 for a flow diagram of the study design.

**Fig. 1 Fig1:**
[figure not shown]
Flow diagram of the study design. ^a^: Patients with colon cancer or dysplasia grade I, II, or III will participate in the prehabilitation program in the time between contemplation of surgery and the procedure, whereas patients with rectal cancer, in case neoadjuvant therapy is needed, will complete the prehabilitation program *prior to* radiotherapy (in case of neoadjuvant radiotherapy, 5 × 5 Gy) or in the twelve-week period *after* neoadjuvant chemoradiotherapy (in week 10-12). Abbreviations: CPET, cardiopulmonary exercise test; MET, metabolic equivalent of task; VAT, ventilatory anaerobic threshold

Patients in the prehabilitation group and the usual care group will be informed differently. The patients in the prehabilitation group will be fully informed about the study in a patient information letter that explains the aims and expectations of this study, as well as the risks and benefits of participating. Patients in the usual care group will not receive information about the possible effects of prehabilitation to avoid the risk that these patients will initiate preoperative physical exercise training themselves. The usual care group will receive a patient information letter about the registration of perioperative data and the hypothesized relation of cardiorespiratory fitness with postoperative complications after colorectal resection. Patients in both the prehabilitation group and the usual care group will be contacted by the clinical research coordinator a few days later to answer their questions, and to inform them about the CPET date. This procedure is approved by the Medical Ethics Committee Twente.

### Randomization

To analyze the effect of a three-week prehabilitation program on postoperative complications, patients with a VSAQ score ≤ 7 will be randomized in the intervention group (prehabilitation) or the control group (usual care) by using block-stratified randomization [37]. Randomization is stratified by disease and treatment type: 1) patients with colon cancer, 2) patients with rectal cancer who will receive one week of neoadjuvant radiotherapy, and 3) patients with rectal cancer who will receive five weeks of neoadjuvant chemoradiotherapy. The clinical research coordinator of the surgical department will be responsible for the randomization. Participants, care providers, and outcome assessors will not be blinded after randomization. However, the data analysts will be blinded to group allocation and are independent to the intervention. After randomization, all participants will perform a CPET for final inclusion, as merely patients with a VAT < 11 mL/kg/min can participate in the study.

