### Measurements

Both the prehabilitation group and usual care group will participate in a series of outcome measure assessments at baseline, seven days postoperatively, and 30 days postoperatively, whereas the prehabilitation group will participate in a series of outcome measure assessments after the three-week prehabilitation program as well (see Table 3).

**Table 3 Tab3:** Schedule of enrolment, interventions, and assessments

STUDY PERIOD	Enrolment	Allocation	Post-allocation					Follow-up	
			Pre-prehabilitation	Prehabilitation			Post-prehabilitation		
TIMEPOINT	-t_1_	0		Week 1	Week 2	Week 3		Day 7 post-surgery	Day 30 post-surgery
ENROLMENT:									
Eligibility screening	X								
VSAQ score (METs)	X								
Informed consent	X								
Allocation		X							
CPET	X								
INTERVENTIONS:									
Intervention group (prehabilitation program)									
Usual care group									
ASSESSMENTS:									
Baseline characteristics	X								
SNAQ score (0-5)	X								
VAT on CPET (mL/kg/min)			X				X^a^		
TUG test (s)			X				X^a^		
Muscle strength test			X				X^a^		
IADL			X						X
GDS 15			X						X
EORTC QLQ-C30			X						
GFI			X						X
Brief illness perception questionnaire			X				X^a^		
EQ-5D			X				X^a^		
Postoperative complications								X	X

^a^: Only for patients in the prehabilitation group

Abbreviations: CPET, cardiopulmonary exercise test; EORTC QLQ-C30, quality of life questionnaire of the European organisation for research and treatment of cancer; EQ-5D, EuroQol 5D; GDS 15, geriatric depression scale 15; GFI, Groningen frailty indicator; IADL, instrumental activities of daily living; MET, metabolic equivalent of task; SNAQ, short nutritional assessment questionnaire; TUG, timed up-and-go; VAT, ventilatory anaerobic threshold; VSAQ, veterans-specific activity questionnaire

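### Final eligibility is settled after unblinded randomisation, and the willingness criterion can in practice be failed only in the prehabilitation arm, so one-arm selection is possible and the ITT set does not clearly prevent it

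*Protocol article*

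**What the plan says.** **Order of steps.** Under Recruitment, patients scoring 7 METs or less on the VSAQ consent on very limited information, are randomised, and then have a CPET. Those with a VAT of 11 mL/kg/min or more leave the study in either arm. The Randomization section gives the same order: "After randomization, all participants will perform a CPET for final inclusion".

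**Blinding.** "Participants, care providers, and outcome assessors will not be blinded after randomization". Only the data analysts are blinded.

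**Information by arm.** The Recruitment section (text after Fig. 1) gives the prehabilitation arm a full information letter. For the other arm, "Patients in the usual care group will not receive information about the possible effects of prehabilitation"; its letter covers data registration and the link between fitness and complications. Patients are telephoned with the CPET date a few days later. The Discussion dates this procedure to an amendment approved in April 2016; before that, both arms were told.

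**Willingness.** Criterion 9 under Participants is "willing to perform prehabilitation at a community physical therapy practice in the adherence area of both hospitals". The same section says that patients who do not meet the criteria are not considered for inclusion.

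**Analysis set.** The Statistical analysis section names an intention-to-treat and a per-protocol population and says that withdrawn patients are followed through their files. It does not say who belongs to the intention-to-treat population.

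**Table 3** ("Schedule of enrolment, interventions, and assessments") marks CPET in the Enrolment column, before Allocation, and marks VAT on CPET in the pre-prehabilitation column, after Allocation.

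**The concern.** Randomisation protects the comparison only if entry to the analysed arms does not depend on allocation. Here two entry conditions are settled once allocation is known.

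Willingness is the more serious of the two. Under the current letters, a usual care patient is not in a position to decline a programme whose purpose has not been explained, whereas a prehabilitation patient is. The Discussion confirms that some patients are unable or unwilling to attend, for reasons of time, distance, transport, holidays or lack of interest. If they are treated as failing criterion 9, the prehabilitation arm loses a self-selected group while its counterparts in usual care stay in. An ITT analysis cannot repair that if these patients never enter the ITT population. The primary comparison, 50% against 20% complications, would then mix the effect of training with the effect of who agreed to train.

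The VAT cut-off is the lesser concern. It is a pre-treatment measure applied to both arms, but the reading allows a choice between two methods and the article states no masking of the reader.

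**Working it through.** **1. The plan's own figure.** Inputs from the Sample size calculation section: 50% against 20%, alpha 0.0492, power 0.80, 1:1 allocation. Two-sided, without continuity correction:

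n = [1.967 × √(2 × 0.35 × 0.65) + 0.842 × √(0.50 × 0.50 + 0.20 × 0.80)]² / 0.30² = 38.7, so 39 per arm.

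This matches the plan. Adding 10% (39 × 1.10 = 42.9) gives its 43. The concern is therefore about design, not arithmetic.

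**2. Who can fail which criterion, and when.**

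| Criterion | When settled | Prehabilitation arm | Usual care arm |
|---|---|---|---|
| VSAQ ≤ 7 METs | before allocation | can fail | can fail |
| VAT < 11 mL/kg/min | after allocation | can fail | can fail |
| Willing to do prehabilitation (letters since April 2016) | after allocation | can fail | in practice cannot |

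**3. Possible size of one-arm selection.** The documents give neither a refusal rate nor a risk among refusers, so both are assumed. Suppose training has no effect, the average risk is 50% (the plan's control rate), a share f of the prehabilitation arm refuses and is removed, and refusers have risk r. The risk among those left is

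p = (0.50 − f × r) / (1 − f),

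and the false effect is 0.50 − p (positive favours prehabilitation). Example: f = 0.30, r = 0.70 gives p = (0.50 − 0.21) / 0.70 = 0.414, a false effect of 8.6 points. The last column is the exact probability that the Pearson test reaches P < 0.0492, two-sided, with 43 analysed per arm.

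| Refusal f | Refuser risk r | p | False effect (points) | Rejection probability |
|---|---|---|---|---|
| 20% | 30% | 55.0% | −5.0 | 0.067 |
| 20% | 40% | 52.5% | −2.5 | 0.049 |
| 20% | 50% | 50.0% | 0 | 0.043 |
| 20% | 60% | 47.5% | +2.5 | 0.049 |
| 20% | 70% | 45.0% | +5.0 | 0.067 |
| 30% | 30% | 58.6% | −8.6 | 0.116 |
| 30% | 40% | 54.3% | −4.3 | 0.060 |
| 30% | 50% | 50.0% | 0 | 0.043 |
| 30% | 60% | 45.7% | +4.3 | 0.060 |
| 30% | 70% | 41.4% | +8.6 | 0.116 |

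With no selection the test rejects 4.3% of the time, so at 20% refusal and 40% or 60% refuser risk it stays within its nominal 4.92%. At 30% refusal and 70% risk, 0.113 of the 0.116 falls on the side favouring prehabilitation; at 30% risk the same share falls on the other side.

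**4. Cost of keeping refusers.** Suppose a share w of the prehabilitation arm refuses but is analysed as allocated, at 50% risk. The arm's rate becomes 0.20 × (1 − w) + 0.50 × w.

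| w | Prehabilitation rate | Exact power, 43 per arm | n per arm for 80% power, before dropout (formula of step 1) |
|---|---|---|---|
| 0 | 20% | 85% | 39 |
| 10% | 23% | 76% | 49 |
| 20% | 26% | 65% | 64 |
| 30% | 29% | 52% | 85 |

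**The case against.** The case for leaving the plan alone is substantial, and most of it stands as a limit on the point.

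- **A reader might infer that refusers are in fact dropped from the prehabilitation arm.** No section says so outright. The Statistical analysis section names intention to treat and follows withdrawn patients through their files, which could keep them. That stands. But the Participants section points the other way, and the ITT population is not defined, so the exclusion is permitted rather than ruled out.
- **A reader might infer that the bias favours prehabilitation.** The documents do not support a direction. The reasons listed in the Discussion are logistical or lack of interest, no rate is given, and a holiday or lack of interest need not mean higher surgical risk. Refusers at lower than average risk would reverse the sign.
- **A reader might infer that the VAT cut-off is itself open to manipulation through effort.** The Background describes VAT as only marginally dependent on motivation, and the Cardiopulmonary exercise test section allows computerised regression and cites acceptable inter-observer variability. Nor does any section say that the reader knows the allocation. What remains is that masked reading is not stated.
- **A reader might take Table 3 as proof that the CPET precedes allocation.** It supports both orders, so it cannot settle which is meant.
- **The one-arm asymmetry covers only part of recruitment.** Before April 2016 both arms were told about prehabilitation. This stands.

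Exclusions after allocation also disturb the balance within blocks, but that alone does not bias the comparison.

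**Conclusion.** The point holds as a design weakness. As written, the procedure allows patients to leave the prehabilitation arm after allocation under a criterion that the usual care arm is in practice not placed to fail, and the ITT wording does not clearly bring them back. Whether this has happened, and how often, cannot be told from the article.

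Under the assumed 20-30% refusal and 30-70% refuser risk, the false effect lies between about −8.6 and +8.6 points, against a planned difference of 30 points. It vanishes if refusers carry average risk. The chance of a false-positive result reaches about 0.12 only in the extreme corners of that range. The finding is therefore that the protection of randomisation is not secured, not that a bias in a known direction has been shown. The VAT exclusion is secondary, and the Table 3 inconsistency is a plain matter of reconciliation.

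**What to change.** 1. Perform the CPET that every consenting patient already undergoes after consent and before randomisation, and randomise only patients with VAT < 11 mL/kg/min. This adds no test and need not reveal prehabilitation to the usual care arm.
2. Do not apply criterion 9 after allocation. Step 1 alone does not solve this half of the problem.
3. Define ITT as every randomised patient with baseline VAT < 11 mL/kg/min, in the allocated arm, whether or not training is accepted or attended. Take outcomes from the patient file where consent allows. Refusers can still be left out of the per-protocol analysis.
4. For patients already randomised, apply the same ITT definition, report post-randomisation exclusions by arm and reason, and state whether the VAT was read without knowledge of allocation.
5. Reconcile the two CPET rows of Table 3 with each other and with the Recruitment and Randomization sections.

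The cost is an amendment to the order of two existing steps and to one definition, plus a real loss of power if refusers are numerous: at 43 per arm, from about 85% to 76%, 65% or 52% with 10%, 20% or 30% refusal at 50% risk. The power statement should be revised using the trial's own refusal count. If 80% is to be kept under those rates, 49, 64 or 85 per arm are needed before dropout.
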